## Abstract

Preterm birth (PTB) is the main cause of perinatal and neonatal morbidity and mortality worldwide. Widespread implementation of guidelines for early identification and management of patients at risk for adverse pregnancy outcomes is still feeble. This work aims to implement a simple and low-cost bundle to access and manage major modifiable risk factors for PTB. We included first trimester pregnant women seen at Health Units from Jaú – SP, Brazil, where PTB prevalence ranges from 13,4% to 18%. The protocol is based on three aspects: a questionnaire to access smoking status and clinical history; Gram staining and of vaginal microbiota evaluation using Nugent’s criteria and evaluation of cervical infections; and transvaginal ultrasound. Pregnant women who smoke and are willing to quit will be treated with auricular acupuncture and referred to a support group if necessary. All patients will be advised on intimate hygiene habits, and those with dysbiosis will be treated. Cervical length will be accessed using transvaginal ultrasound, and those diagnosed with cervical shortening will be treated with vaginal progesterone. This study highlights the importance of implementing active measures to reduce PTB risk factors in a high prevalence setting.

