## Background

Preterm birth (PTB), defined as birth before 37 weeks of gestation, is associated with perinatal morbidity and mortality worldwide. Preterm newborns are more likely to have short- and long-term complications, such as neurological impairment and increased susceptibility to infections, which can lead to irreversible sequelae and reduced quality of life [1].

Worldwide, the prevalence of PTB is approximately 11% [1], and Brazil is one of the most affected countries, with over 308,700 children born preterm every year, accounting for a preterm birth rate of 11.5%. In São Paulo state, 12% of births in 2023 were preterm, and a higher percentage was reported in the municipality of Jaú, where this adverse outcome affected 13.5% of all pregnancies [2].

PTB is a syndrome of multifactorial etiology with significant activation of inflammatory, oxidative stress, and senescence pathways [3]. PTB prevention should be a priority in public health policies; however, despite all the scientific and clinical efforts to fully elucidate and prevent PTB, protocols for early identification and effective management of women at risk have not yet been well-defined or effectively implemented, especially in Brazil. The main barrier to the implementation of such strategies is the gap in knowledge and communication between researchers, health professionals, and policymakers. In this context, three modifiable risk factors stand out for their well-established association with PTB: smoking habit, vaginal dysbiosis, and cervical shortening [4–9].

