**Figure 1. f0001:**
[figure not shown]
Temporal flowchart of cluster inclusion (health units) in the quasi-experimental design study.

During the first 18 months, all first-trimester pregnant women from eight randomized UBS/USF (clusters) are being included. In the next step of the study, 2 UBS/USF per month will be included until all primary care units (clusters) in the municipality are included, as demonstrated in Figure 1.

All pregnant women of eligible gestational age from the eight initially randomized health units were systematically invited to participate in the study and referred to Gestar. Cluster randomization was performed using a randomization tool (https://www.random.org/). Allocation was concealed and known exclusively by the coordinating researcher until implementation, minimizing the risk of selection bias. All participants included in the study will be monitored until the gestational outcome through three appointments, one in each gestational trimester. The inclusion criteria for the study are singleton pregnancy and gestational age between 11 weeks and 13 weeks and 6 days at the first appointment, defined by ultrasound. Pregnancies with fetal death and those attending fewer than two study appointments (first and second trimester) will be excluded from the study.

Considering the intervention aims to reduce the preterm birth rate from 18% (baseline rate, DataSUS) to 11.5% (São Paulo state rate = target rate), with 95% confidence, 5% margin of error, and 80% statistical power, the minimum sample size calculated is 201 patients (SAS 3.0 software). Adjusting the sample size to account for cluster effects (DE = 1+(m − 1)×ICC, where DE: design effect; mean cluster size: *m* = 20; intra-cluster correlation coefficient: ICC = 0.01), the conventional individual-based sample of 201 increased to 240. Considering a 20% loss to follow-up, the final sample size will be 300 participants.

To reduce cross-contamination, clinical procedures are centralized at a reference site (Gestar), and the distribution of printed and digital protocols to the Health Units are restricted until activation. A 2-week operational wash-in with adherence monitoring was implemented.

This project was approved by the Research Ethics Committee of Unoeste – Universidade do Oeste Paulista (CAAE 63,623,922.70000.5515). All patients involved will be informed about the research and sign the informed consent form.

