### Analysis plan

The main outcome of interest is gestational age at birth, based on first-trimester ultrasound, to be compared between the participants of the study and the general population. For the analysis, gestational age will be treated as categorical data (preterm birth vs. term birth). The primary analysis will follow the intention-to-treat principle: participants will be analyzed according to the assignment of their cluster at the time of inclusion. Secondary analyses will consider gestational age at delivery (continuous, in days) and other perinatal outcomes.

Secondary outcomes include the percentage of pregnant women included, the percentage of complete follow-up, percentage of adherence to prescribed treatments, and neonatal outcome (Apgar score, birth weight, and length of stay in the Intensive Care Unit). Descriptive statistics will be performed to analyze clinical, biological, and sociodemographic data of the studied population. Vaginal microbiota status across the trimesters will be compared using the Chi-square test.

Logistic regression will be performed to evaluate the role of the protocol in reducing PTB. To minimize multiplicity in the analysis and interpretation, covariates for adjustment such as parity, maternal age, and socioeconomic status will be included. The primary effect estimate will be obtained from mixed-effects logistic regression models including a random intercept for cluster and fixed effects for period and pre-specified baseline covariates (maternal age, parity, socioeconomic status). Additional per-protocol analyses will be performed as sensitivity analyses and will include participants who received the defined intervention components. Missing data in covariates will be handled using multiple imputations (MICE) under a missing-at-random assumption. The level of significance adopted for the tests used will be 5%, using *Prism* 5.0 (GraphPad Software).

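### The sample-size rates do not match the article's own figures: 11.5% is called the São Paulo state rate but is given elsewhere as Brazil's, and the 18% baseline is the unexplained top of the stated range

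*Protocol article*

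**What the plan says.** The sample-size paragraph in Methods, Study design, sets the aim of the calculation as to "reduce the preterm birth rate from 18% (baseline rate, DataSUS) to 11.5% (São Paulo state rate = target rate"). The accompanying precision and power settings are a 95% confidence level, a 5-point margin of error and a power of 80%. The paragraph arrives at 201 women, raises this to 240 for clustering (mean cluster size 20, ICC 0.01) and to 300 for a 20% loss to follow-up.

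Three other statements bear on the two rates:

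- Background, on Brazil: "accounting for a preterm birth rate of 11.5"%.
- Background, on the state: "In São Paulo state, 12% of births in 2023 were preterm". The figure for Jaú stands later in that sentence: "where this adverse outcome affected 13.5% of all pregnancies".
- Abstract, on Jaú: "where PTB prevalence ranges from 13,4% to 18"%.

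The sample-size paragraph attributes 18% to DataSUS. It gives no year or population for it and no reason for preferring it to 13.5%.

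**The concern.** The two rates have different problems.

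The target is a plain inconsistency. The same number, 11.5%, is Brazil's rate in the Background and the state's rate in the Methods, and the Background gives the state 12%. Both statements cannot be right.

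The baseline is an unexplained choice. It lies 4.5 points above the Background figure for the municipality and at the upper limit of the Abstract's range. The higher the baseline, the larger the planned reduction and the smaller the sample: 18% to 11.5% is 6.5 points, whereas 13.5% to 11.5% is 2.0 points and 13.5% to 12% is 1.5 points.

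The 201, 240 and 300 and the stated 80% power all rest on these two rates. If the participating units are nearer 13.5% than 18%, the trial has far less power to show a fall to the named target than a reader would suppose.

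**Working it through.** **Inputs.** Rates 18%, 13.5%, 13.4%, 12% and 11.5% (Abstract, Background, Methods); 80% power; n = 201, 240 and 300 (Methods). The Analysis plan states the test level: "The level of significance adopted for the tests used will be 5"%. Sidedness and allocation ratio are not stated, so two simple designs are used and both are assumptions. Neither is the stepped-wedge design that the article describes. They serve to show how strongly the answer depends on the rates.

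**The plan's own figures.** The later steps reproduce: design effect 1 + 19 × 0.01 = 1.19; 201 × 1.19 = 239.2, so 240; 240 / 0.8 = 300. The 201 itself is not reproduced by any two-group variant tried. The closest reading is one sample, one-sided, against a fixed 18%: 192, or 207 with continuity correction. That is a separate matter. It is noted here only because it explains why a one-sample reading is also shown.

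**Check 1: two equal groups, two-sided 5%, 80% power, no clustering.**

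n per group = [1.96·√(2p̄(1−p̄)) + 0.8416·√(p₁(1−p₁) + p₂(1−p₂))]² / (p₁−p₂)², with p̄ the mean of the two rates.

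Example, 18% to 11.5%: p̄ = 0.1475; the roots are 0.5015 and 0.4994; [1.96 × 0.5015 + 0.8416 × 0.4994]² / 0.065² = 466.01, rounded up to 467.

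| Baseline to target | Gap (points) | n per group | Relative to plan |
|---|---|---|---|
| 18% to 11.5% | 6.5 | 467 | 1 |
| 18% to 12% | 6.0 | 555 | 1.2 |
| 13.5% to 11.5% | 2.0 | 4,292 | 9.2 |
| 13.5% to 12% | 1.5 | 7,761 | 16.6 |

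At the bottom of the Abstract's range, 13.4% to 11.5% needs 4,739 per group and 13.4% to 12% needs 8,879.

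**Check 2: one sample of 201 against a fixed rate p₀, true rate p₁.** The 240 women left after loss, divided by the design effect of 1.19, are worth about 201 independent women.

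Power = Φ{[(p₀−p₁)·√n − z·√(p₀(1−p₀))] / √(p₁(1−p₁))}, with z = 1.96 two-sided or 1.645 one-sided.

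Example, 18% to 11.5%, two-sided: (0.065 × 14.177 − 1.96 × 0.3842) / 0.3190 = 0.53, so power is 70%. Example, 13.5% to 11.5%, two-sided: (0.020 × 14.177 − 1.96 × 0.3417) / 0.3190 = −1.21, so power is 11%.

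| Baseline to target | Power, two-sided | Power, one-sided |
|---|---|---|
| 18% to 11.5% | 70% | 82% |
| 18% to 12% | 62% | 75% |
| 13.5% to 11.5% | 11% | 19% |
| 13.5% to 12% | 8% | 14% |

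**Smallest detectable reduction on the same one-sample reading.** Solving the power formula for p₁ at 80% power, two-sided, with n = 201 gives about 10.8% from a baseline of 18% and about 7.2% from a baseline of 13.5%. The second value is far below any target that the article names.

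**The case against.** The strongest reply is that 18% is not contradicted. It lies inside the Abstract's range and is sourced to DataSUS. The 13.5% describes all pregnancies in the municipality, in a sentence about 2023, whereas the 18% may refer to another year or population. This stands: the documents show an unexplained and favourable choice of baseline, not a figure proved wrong. What remains is that the reader cannot tell why the top of the range was taken.

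It is also fair that the certain error, the label, has a modest effect: 467 to 555 per group, about 19%. The 9- and 17-fold increases come from replacing 18% with 13.5%, which is the arguable step. And the magnitudes depend on designs that the article does not state.

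Three stronger readings are tempting, and the documents do not support them:

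- *18% is the benchmark for success, so an inert bundle would look effective.* The Analysis plan mentions a comparison with the general population but does not fix that population's rate at 18%. Its primary estimate comes from a mixed-effects logistic model with period effects. Even if a true rate of 13.5% were tested against a fixed 18% with n = 201, rejection would occur in about 37% of trials two-sided, which is not assured.
- *The effect cannot be detected.* Power of 8% to 19% means badly underpowered if 13.5% is the true baseline, and no more than that.
- *The baseline must be lower still because only singletons are enrolled.* The article gives no preterm rate by plurality, so no figure can be put on this.

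**Conclusion.** The point holds. The label on the target is wrong by the article's own figures, and the baseline is the most favourable value in the article's range with no reason given. The stated 80% power holds at best at the top of that range. The label alone is a moderate matter; the baseline decides whether the sample is roughly adequate or far too small.

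The direction is the same under both simple designs, one- or two-sided. The exact sizes rest on 1:1 allocation without clustering for the two-group figures, and on a known fixed comparator rate with 201 effective women for the one-sample figures. A proper stepped-wedge calculation would give other numbers. It would still start from the same two rates and would need them settled first.

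**What to change.** 1. Correct the target: either label 11.5% as the Brazilian rate, or keep the state rate as the target, use 12% and recalculate.
2. State the year and population behind the 18% and why it was chosen. Otherwise base the calculation on the most recent preterm rate for the participating units.
3. Restate the power of the planned 300 participants across baselines from 13.4% to 18%, naming the design and sidedness assumed, and give the smallest reduction detectable with 80% power at each baseline.

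This takes a few sentences and a short power table and changes no trial procedure. The price is that the stated power becomes less favourable, and if the units prove to be near 13.5% the authors will have to say that a fall to the named target is unlikely to be shown with 300 women. Because the study is ongoing, the restatement should be made before outcomes are analysed.

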## Methods

### Study design

This is the protocol of an ongoing implementation study with a quasi-experimental controlled trial design conducted with pregnant women from primary health care units in the municipality of Jaú. The city of Jaú, located in the central region of the state of São Paulo, has a population of 151,881 inhabitants and 16 Basic Health Units (UBS) and Family Health Units (USF), in addition to a high-risk pregnancy clinic, Gestar, where this project is implemented.

The 16 UBS/USF were considered clusters and will be included in the study at different stages, according to the stepped wedge model, in which the clusters are gradually transferred to the intervention group at regular intervals until all have been transferred. This design is particularly useful in situations where the intervention cannot be implemented simultaneously for all units due to time, logistics, or ethical constraints [10]. In the first phase, eight of these clusters were randomly selected using a simple randomization process to receive the intervention, focusing on pregnant women during their first trimester. Over time, the remaining clusters will be randomly assigned to transition into the intervention group at regular intervals, using the same simple randomization method, ensuring that by the end of the study, all clusters will have received the intervention (Figure 1). This approach allows for a structured, phased implementation of the intervention, accommodating logistical and ethical constraints, and enables the comparison between clusters that have and have not yet received the intervention during the initial stages of the study.

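### The planned 300 women do not give 80% power for the controlled comparison that the primary model estimates; under the stated rates, power lies between about 25% and 70%

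*Protocol article*

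**What the plan says.** The sample-size paragraph (Methods, Study design) takes a baseline preterm birth rate of 18% and a target of 11.5%, and states that "with 95% confidence, 5% margin of error, and 80% statistical power, the minimum sample size calculated is 201 patients". With a mean cluster size of 20 and "intra-cluster correlation coefficient: ICC = 0.01", "the conventional individual-based sample of 201 increased to 240". A 20% allowance for loss gives 300.

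The same section describes a stepped-wedge roll-out over 16 health units and says that the design "enables the comparison between clusters that have and have not yet received the intervention during the initial stages of the study". On accrual it says: "During the first 18 months, all first-trimester pregnant women from eight randomized UBS/USF (clusters) are being included". The other eight units then join at two per month.

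The Analysis plan takes the primary effect estimate from a mixed-effects logistic regression with a random intercept for cluster and fixed effects for period and baseline covariates. It also says, in its opening sentence, that the outcome is compared between participants and the general population.

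**The concern.** A fall from 18% to 11.5% is 6.5 percentage points. Two-group comparisons of that size usually need several hundred women per group, so 201 looks too small for a controlled design. The paragraph names no test, sidedness, number of groups or allocation. It also places a margin of error, which is an input to a precision calculation for a single proportion, beside a power of 80%.

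The trial's primary aim is to reduce preterm birth. If true power is well below 80%, a non-significant result is likely even when the bundle achieves its full target, and the printed 80% would lead readers to take that result as evidence that the bundle does not work.

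**Working it through.** **Inputs.** From the sample-size paragraph: p0 = 0.18, p1 = 0.115, d = 0.065, power 80%, ICC 0.01, m = 20, loss 20%. The Analysis plan sets the significance level at 5%. Sidedness is not stated; two-sided is assumed, with one-sided shown as well.

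**The plan's later steps reproduce.**
- DE = 1 + (20 − 1) × 0.01 = 1.19
- 201 × 1.19 = 239.2, stated as 240
- 240 / 0.8 = 300

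**The starting figure, as a two-group comparison.** Pooled rate p̄ = (0.18 + 0.115)/2 = 0.1475.

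n per group = [1.96 × √(2 × 0.1475 × 0.8525) + 0.8416 × √(0.18 × 0.82 + 0.115 × 0.885)]² / 0.065²
= (0.9829 + 0.4203)² / 0.004225 = 466.01, so 467.

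- With continuity correction: 497 per group.
- One-sided: 367 per group.
- With DE 1.19: 467 × 1.19 = 555.7, so 556 per group.
- With 20% loss: 556 / 0.8 = 695 per group, or 1,390 in total.

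No two-group form gives 201, as a total or per group.

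**The starting figure, as one sample against a fixed 18%.**

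| Test | Two-sided n | One-sided n |
|---|---|---|
| Score | 247 | 192 |
| Score, continuity-corrected | 262 | 207 |
| Arcsine | 231 | 182 |
| Arcsine, continuity-corrected | 246 | 197 |
| Exact binomial | 238–264 | 189–208 |
| Wald, variance at 11.5% | 189 | 149 |
| Wald, variance at 11.5%, continuity-corrected | 204–205 | 164 |

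Some of these come near 201, but all of them treat 18% as a known constant and have no control group.

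**The margin of error.** The precision formula 1.96² × p(1 − p) / 0.05² gives 227 at 18% and 156 at 11.5%. It contains no power term and gives 201 at neither rate.

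**Power that the planned size delivers.** 300 enrolled × 0.8 = 240 analysed; 240 / 1.19 is about 201 effective women. Two-sided 5%, no period effects:

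| Reading of the 300 | Power |
|---|---|
| Both conditions together, effective women split 1:1 | 25% |
| Intervention women only, 201 effective controls | 45% |
| Intervention women only, 1,000 controls | 63% |
| Intervention women only, unlimited controls (score test against a fixed 18%) | 70% |

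For the first row, with 100.5 per group: (0.065 − 1.96 × 0.05002) / 0.04981 = −0.66, and Φ(−0.66) is about 0.25. In the rows with 1,000 and unlimited controls, no clustering is applied to the controls.

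**Secondary: cluster size.** If all 240 analysed women came from the eight units that enrol for the first 18 months, m = 240/8 = 30 and DE = 1 + 29 × 0.01 = 1.29. Then 201 × 1.29 = 259.3, and 259.3 / 0.8 gives about 324 in place of 300.

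**The case against.** The best defence is that the calculation was a one-sample one. The Analysis plan does mention a comparison with the general population, and a two-sided Wald test against a fixed 18%, with variance at 11.5%, needs 189 women; 201 would give it 82% power. A reader might infer that 201 fails for every two-sided comparison, and that is not so. The defence still does not rescue the stated power. Such a test has no concurrent controls and no period effects, whereas the primary estimate comes from a model that needs both. The more usual two-sided one-sample tests need 231 to 264 women, and 201 gives them about 70%.

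A reader might also take 25% as the trial's power. That holds only if the 300 span both conditions in equal numbers, which the article does not say. The women it describes as included come from active units and attend study visits, so the 300 may all be intervention women, and the higher figures then apply.

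It is tempting to explain 201 as a precision calculation with a finite-population correction for roughly 1,770 births. The article gives no such population; the number has to be chosen to reach 201, so nothing here rests on it.

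On cluster size, m = 20 is close to 300/16 = 18.75, so it fits a study in which all 16 units contribute similar numbers. The staggered roll-out makes that unlikely, but the recruitment end is not given and the effect is modest.

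Finally, an article may leave detail to a fuller plan. The point here is a printed size and power that do not fit the printed primary analysis, not missing detail.

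**Conclusion.** The concern holds for the controlled comparison. At 18% versus 11.5%, two-sided 5% and 80% power, about 467 women per group are needed before clustering and loss, and about 695 per group after the plan's own allowances. The planned 300 give between about 25% and 70% power, depending on an allocation that the article does not state. The upper figure is a ceiling for a score-type test with unlimited controls. All these figures assume the stated rates, the stated ICC and a simple parallel comparison; none includes the period effects of the primary model, and the stepped-wedge layout has not been modelled. The design-effect point is real but secondary: about 324 in place of 300 in the case where all analysed women come from the first eight units.

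**What to change.** Rewrite the sample-size paragraph:

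- Name the comparison, the test, its sidedness, the number of groups and the allocation, and say whether 300 counts intervention women only or both conditions.
- Remove the margin of error.
- Recompute for the stepped-wedge model with the actual roll-out (eight units for 18 months, then two per month), cluster sizes that match it, and period effects.
- Report the power that 300 participants deliver in place of 80%.
- State whether eligible births in the waiting units serve as controls. If they do, treat about 70% as a ceiling under the stated rates, not as an expected value.
- If power is below 80%, say so, and present the effect estimate with its confidence interval as the main result.

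The study is ongoing, so this can be done before analysis. It needs a rewritten paragraph and a new calculation, with no extra enrolment. The downside is a less favourable stated power.

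### The design effect of 1.19 comes from a parallel-trial formula with a mean cluster size of 20 that does not fit the stepped-wedge roll-out; closure by month 22 gives about 1.22 to 1.29, a small shortfall

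*Protocol article*

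**What the plan says.** Everything about size and calendar is in Methods, Study design, in the paragraphs after Figure 1.

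- Base: the aim is to "reduce the preterm birth rate from 18% (baseline rate, DataSUS) to 11.5% (São Paulo state rate = target rate"), and "with 95% confidence, 5% margin of error, and 80% statistical power, the minimum sample size calculated is 201 patients".
- Cluster adjustment: "DE = 1+(m − 1)×ICC, where DE: design effect", with "mean cluster size: *m* = 20" and "intra-cluster correlation coefficient: ICC = 0.01". As a result "the conventional individual-based sample of 201 increased to 240". A 20% loss then gives 300.
- Calendar: "During the first 18 months, all first-trimester pregnant women from eight randomized UBS/USF (clusters) are being included". After that, "2 UBS/USF per month will be included until all primary care units (clusters") have joined.
- Comparator: Study design describes comparing units that have the intervention with units still waiting for it. The Analysis plan says participants are compared with the general population. It also specifies a mixed logistic model with a random cluster intercept and fixed period effects.

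The article gives no enrolment rate per unit and no date on which enrolment closes.

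**The concern.** The formula with one value of m is exact for a parallel trial with equal clusters. This plan declares a stepped wedge, its primary model contains period terms, and its calendar gives eight units an 18-month head start over the other eight. When sizes differ, the formula needs the size-weighted mean Σm²/Σm, which always exceeds the plain mean. In a stepped wedge, the variance also depends on how treatment is spread over periods.

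The step from 201 to 240 has one purpose: to keep the stated 80% power in the presence of clustering. If the design effect is too low, the power attached to 300 participants is slightly overstated.

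**Working it through.** **1. The plan's own chain.** 1 + (20 − 1) × 0.01 = 1.19. 201 × 1.19 = 239.2, rounded to 240. 240 / 0.8 = 300. All three figures reproduce.

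**2. Where 20 could come from.** 300/16 = 18.75; 240/16 = 15; 300/8 = 37.5; 240/8 = 30; 16 × 20 = 320. None of the totals gives 20.

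**3. Assumptions for the recalculation.** Equal accrual per unit-month; ICC 0.01 and base 201 as stated; cluster sizes taken among the 240 analysed. Power uses the plan's own base with a two-sided 5% test (the article does not state sidedness): Φ[(1.96 + 0.8416) × √(n_eff/201) − 1.96], where n_eff = 240/DE.

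**4. Only activated units contribute, closure at month 22.**
- Unit-months: 8 × 22 = 176 for the first eight units, and 2 × (4 + 3 + 2 + 1) = 20 for the rest. The total is 196, so the first eight hold 176/196 = 90%.
- Of 240 women, each of the first eight units has about 27. The later pairs have about 5, 4, 2 and 1 per unit.
- Sum of squared unit-months: 8 × 22² + 2 × (16 + 9 + 4 + 1) = 3,932. Size-weighted m = 240 × 3,932/196² = 24.6.
- DE = 1 + 23.56 × 0.01 = 1.236. Need: 201 × 1.236 = 248.4, so 249 analysed and 312 enrolled.
- If cluster sizes grow with the sample, n = 201 × 0.99 / (1 − 2.01 × 3,932/196²) = 250.5, so 251 analysed and 314 enrolled.
- With 240 analysed, n_eff = 240/1.236 = 194 and power is about 78.6%.
- Effective number of clusters: 196²/3,932 = 9.8, for this closing date only.

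**5. All women come from the first eight units** (the target is met within the 18 months). m = 240/8 = 30; DE = 1 + 29 × 0.01 = 1.29; n_eff = 186; power about 77%.

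**6. Waiting units followed as controls from month 0.** I used the random-intercept stepped-wedge variance with fixed period effects, 16 equal-accrual units and periods of 18, 1, 1, 1 and 1 months. It was divided by the variance of a 1:1 individually randomised comparison of the same total size. At 240 the ratio is 1.22. With the ICC set to zero it is 1.093, so the clustering part is 1.22/1.093 = 1.12, and the rest is treatment imbalance and period terms. n_eff = 240/1.22 = 197; power about 79%.

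**7. Later closure, at 240 analysed.**

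| Closing month | DE, activated units only | DE, waiting units as controls |
|---|---|---|
| 22 | 1.236 | 1.22 |
| 25 | 1.202 | 1.37 |
| 26 | 1.194 | not computed |
| 27 | 1.188 | not computed |
| 28 | 1.183 | 1.51 |

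On the first reading 1.19 is reached at about month 26 to 27. On the second, the ratio rises with later closure, because the added months have every unit on the intervention and so add no contrast within a period.

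**The case against.** The strongest defence is that nothing in the stated arithmetic is wrong, and that the shortfall depends on assumptions the article does not make. Most of this stands.

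- A reader might infer that the plan assumes 20 women in every unit. It does not: it calls 20 a mean, and as a plain mean over 16 units 20 is slightly conservative against 15 or 18.75. That margin does not cover the imbalance in step 4.
- A reader might take the 90% share as part of the stated roll-out. It is derived, and needs equal accrual, closure at month 22 and no control women among the participants. So 1.19 cannot be called understated without conditions.
- A reader might size clusters on the 300 enrolled and reach a design effect near 1.30. That mixes two totals: women lost to follow-up add no correlation among the 240 analysed.
- A reader might read 1.22 in step 6 as a clustering effect. Only about 1.12 of it is, so on that reading the clustering part alone lies below 1.19. The defence does not go further, though. The plan applies a single multiplier to an individual-based sample, and under its own model that multiplier must also carry the imbalance and period terms.
- A reader might conclude that the 16 clusters are really about 10. That holds only for closure at month 22, and the article states no degrees-of-freedom rule based on 16.

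It is also fair to say that about one to three points of power is small beside the uncertainty in an assumed ICC of 0.01.

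**Conclusion.** The point holds in a limited form. The plan's figures follow from its formula, but the formula and m = 20 do not describe the declared design. With equal accrual per unit-month and closure by month 22, the design effect is about 1.22 to 1.29 rather than 1.19, and 240 analysed women give about 77% to 79% power on the plan's own base. On the activated-units-only reading the need is about 249 to 251 analysed, or 312 to 314 enrolled, which is 4% to 5% more than planned. That reading makes 1.19 adequate once enrolment runs to about month 26 or 27. The article does not settle which reading applies. All of this takes 201 as given; whether 201 follows from its stated inputs is a different and separate matter.

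**What to change.** In the sample-size paragraph:

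1. State whose data count towards the 240 and 300 (activated units only, or also women in waiting units), and the planned closing date. Make this agree with the comparator in the Analysis plan.
2. Replace 1 + (20 − 1) × 0.01 with the stepped-wedge variance for that calendar. If only activated women count, use the size-weighted mean cluster size at the analysed number instead.
3. Keep 300 participants. Restate the design effect (about 1.22 to 1.29 for closure by month 22) and the slightly lower power that 240 analysed gives.
4. If an effective number of clusters is reported, tie it to the closing date (about 10 for month 22 with activated units only).

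The cost is a reworded paragraph and a slightly less favourable power figure. No extra participants are needed if the figure is simply restated.
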